### Participant timeline {13}

**Table Tabc:**
[figure not shown]

^**^Statistical significant

### Sample size {14}

#### Sample size: calculation for comparing two means at pain severity using VAS

##### Formula used

The formula for calculating the sample size for comparing two means is:$$n\geq\left[\left(Z\_\left\{1-\alpha/2\right\}+Z\_\left\{1-\beta\right\}\right)^2\cdot\left(\upsigma_1{}^2+\upsigma_2{}^{2/r}\right)\right]/\left(\mu_2-\mu_1\right)^2$$where:*Z*_{1-*α*/2} is the *Z*-score corresponding to the two-sided significance level.*Z*_{1-*β*} is the *Z*-score corresponding to the desired power.σ_1_^2^ and σ_2_^2^ are the variances of the two groups.*r* is the ratio of the group sizes.(*μ*_2_—*μ*_1_) is the difference in means between the two groups.Alpha (*α*): 0.05 (significance level) = 1.96Beta (*β*): 0.2 (power = 1—*β* = 0.8) = 0.084Mean in group 1 (*μ*_1_): 7.916 (A s per reference article)Standard deviation in group 1 (σ_1_): 2.256Mean in group 2 (*μ*_2_): 5.983Standard deviation in group 2 (σ_2_): 2.327Ratio of group sizes (group 2/group 1): 1:1

##### Results

Minimum sample size needed for group 1: 23Minimum sample size needed for group 2: 23Total sample size required: 46

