**Methods:**

Forty-six LSCS subjects with pain, urine incontinence, sleep quality, and activities of daily life will participate in a comparative study that is a blinded (statistical) analysis. The participants will be divided into two groups following randomization: (1) Benson’s relaxation and (2) Mitchell’s relaxation, and both groups will receive exercises from conventional physiotherapy. Every group will go through the initial evaluation and a post-intervention assessment.

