### Methods in analysis to handle protocol non-adherence and any statistical methods to handle missing data {20c}

Not applicable.

For subjects who finish the research, the protocol mainly concentrates on pre- and post-intervention analyses, and all analyses are designed for participants who finish the pre- and post-intervention questionnaires.

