## Discussion

In order to assess the efficacy of Benson’s and Mitchell’s relaxation techniques, each in conjunction with conventional physiotherapy, for women recovering from lower segmental cesarean sections (LSCS), the protocol offers a carefully planned, single-blind, randomized comparative clinical trial. This study’s justification stems from the high and increasing prevalence of LSCS worldwide, which is linked to serious postpartum problems such as pain, urinary incontinence, sleep issues, and diminished capacity to carry out everyday tasks. Comprehensive rehabilitation is necessary since these issues affect not only physical healing but also psychological and social well-being.

Both Mitchell’s and Benson’s relaxation methods are well-researched psychophysiological therapies that have been demonstrated to enhance sleep quality and lessen stress, pain, and anxiety in a variety of populations. Nevertheless, there is a dearth of direct comparison data about their efficacy in LSCS patients. In order to fill this gap, the procedure enlists 46 women between the ages of 20 and 40. They are then randomly randomized to receive either Benson’s or Mitchell’s relaxation technique in addition to conventional physiotherapy exercise. Five days a week, for 30 min per session, the interventions are given under supervision to guarantee proper technique and adherence. This strategy minimizes confounding variables while enabling a strong comparison.

The visual analogue scale (VAS) for pain, the incontinence severity index (ISI) for urine incontinence, the Pittsburgh Sleep Quality Index (PSQI) for sleep quality, and the Barthel Index for activities of daily living are among the extensive and validated outcome measures used in this study. These instruments will be employed both before and after the intervention, allowing for a comprehensive evaluation of the methods’ effects on important facets of postpartum recuperation. Careful attention is paid to ethical issues: all participants provide their informed consent, and precise inclusion and exclusion standards are set up to guarantee participant security and data integrity. Both procedures are safe and non-invasive, and the protocol permits stopping them if there is any discomfort or unfavorable outcome. Education, demonstration, and supervised sessions are some strategies to increase adherence, which are essential for guaranteeing consistent implementation of the interventions and trustworthy outcomes.

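### The 46 women to be enrolled are the uninflated minimum for 80% power, yet only completers are analysed, so the stated power leaves almost no room for loss

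*Protocol article*

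**What the plan says.** Section {14} of the protocol article, under Formula used, compares two VAS means with a Z value "corresponding to the two-sided significance level", alpha 0.05, power 0.8, and means and SDs taken from a reference article. Its Results paragraph concludes: "Minimum sample size needed for group 1: 23Minimum sample size needed for group 2: 23Total sample size required: 46". No adjustment for loss is shown.

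The same 46 appears as the number entering the trial. The Abstract says "Forty-six LSCS subjects with pain, urine incontinence, sleep quality, and activities of daily life will participate", and the Discussion says "the procedure enlists 46 women between the ages of 20 and 40".

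Section {20c} marks methods for non-adherence and missing data as not applicable and adds that "all analyses are designed for participants who finish the pre- and post-intervention questionnaires". The between-group test is an independent t-test, or a Mann–Whitney test if the data are not normal (section {20a}).

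**The concern.** The formula returns the number of women whose VAS values must be in the comparison for 80% power. Under the rule in {20c}, a woman without a week-4 questionnaire is not in the comparison. If 46 enter and some are not assessed at week 4, the analysed number falls below the stated minimum, and the 80% no longer describes the sample that is tested.

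What is at stake is how the result is read. A non-significant difference in VAS would be judged against 80% power when the analysed sample may have less. The point concerns the stated power only, not possible bias in a completers analysis.

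**Working it through.** **Inputs**, all from section {14}, Formula used: means 7.916 and 5.983 (difference 1.933); SDs 2.256 and 2.327; two-sided alpha 0.05 (Z = 1.96); power 0.80; ratio 1:1.

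**Step 1: reproduce the plan's figure.** n per group = (Zα + Zβ)² × (σ1² + σ2²) / (difference)².

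- σ1² + σ2² = 2.256² + 2.327² = 5.090 + 5.415 = 10.504
- difference² = 1.933² = 3.736
- Zβ = 0.84: 2.80² × 10.504 / 3.736 = 22.04, rounded up to 23 (with Zβ = 0.8416, 22.07, also 23)
- Zβ = 0.084, as printed: 2.044² × 10.504 / 3.736 = 11.75, rounded up to 12

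The stated 23 per group and 46 in total therefore come from 0.84, with no inflation for loss.

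**Step 2: power for the number analysed.**

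- Normal formula: power = Φ(1.933 / SE − 1.96), with SE = √(σ1²/n1 + σ2²/n2). At 23/23, SE = √(10.504/23) = 0.676, so power = Φ(2.860 − 1.96) = Φ(0.900) = 81.6%.
- t-test: noncentral t with n1 + n2 − 2 degrees of freedom and standardised difference 1.933 / √(10.504/2) = 1.933 / 2.292 = 0.843.

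| Analysed (group 1/group 2) | Normal formula | t-test |
|---|---|---|
| 23/23 | 81.6% | 79.9% |
| 23/22 | 80.7% | 79.0% |
| 22/22 | 79.9% | 78.0% |
| 21/21 | 78.0% | 76.0% |
| 21/20 | 77.0% | 74.9% |

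**Step 3: assumed loss rates.** The article gives none, so 10% and 20% serve as illustrations, with loss equal in the two groups.

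| Loss | Analysed per group (average) | Normal formula | t-test |
|---|---|---|---|
| 10% | 23 × 0.90 = 20.7 | 77.4% | 75.4% |
| 20% | 23 × 0.80 = 18.4 | 72.5% | 70.1% |

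Against a nominal 80%, the shortfall at 10% loss is 2.6 points (normal) or 4.6 points (t-test). At 20% it is 7.5 or 9.9 points. The two methods differ by about 1.7 to 2.4 points over this range, so the method must be named beside any restated figure.

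**The case against.** The strongest reply is that the arithmetic is right and the text is not contradictory. The stated 23 reproduces, and enrolling the computed number is consistent across the Abstract, section {14} and the Discussion. The article never says that 46 is a minimum number analysed; that follows only when section {14} is read with {20c}. An allowance for loss might also stand in a fuller protocol. Part of this holds: it is an unallowed-for loss, not a calculation error. But the calculation is printed in full, and the enrolment figure and the completers rule are both stated, so the consequence for power can be judged from the article itself.

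A reader might infer more than the document supports:

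- **That 80% power holds only if nobody is lost.** On the plan's own formula, rounding 22.04 up to 23 leaves room for one loss, and with two (22/22) power is still 79.9%. On the t-test, 80% is narrowly missed even with no loss.
- **That section {11b} predicts loss.** It concerns stopping or altering the intervention. A woman who stops the relaxation sessions can still complete the week-4 questionnaires and be analysed.
- **That substantial loss is to be expected.** The document gives no rate, follow-up lasts 4 weeks, and section {18b} plans daily contact and two defined assessment points. These do not guarantee full retention, but they count against presuming a large loss.
- **That the printed 0.084 undermines the sample size.** It would give 12 per group, whereas the stated 23 requires 0.84. It is a misprint that did not feed into the result.

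**Conclusion.** The point holds in a limited form. Forty-six is the uninflated requirement and also the number enrolled, while analysis is confined to completers. The stated 80% therefore has room for at most one or two losses on the plan's normal formula and none on the planned t-test.

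The likely effect is modest: about 77% or 75% power at 10% loss, and about 73% or 70% at 20% (normal formula and t-test respectively). These figures rest on the plan's own difference and SDs, on roughly equal loss in the two groups, and on loss rates that are assumptions. This is a correction to how the power is described. The documents do not show that the enrolment target has to change.

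**What to change.** In section {14}:

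- State that 46 is the number enrolled and contains no allowance for loss.
- Restate VAS power for the number expected to be analysed, with the method and the assumed loss rate. For example: about 77% (normal formula) or 75% (t-test) if about 10% do not complete week 4, and about 73% or 70% if about 20% do not. Replace these illustrative rates if the investigators have a better basis.
- As a separate correction, change the printed Z for power from 0.084 to 0.84.

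The cost is a few sentences and a slightly less favourable stated power. Enrolment, procedures and the analysis stay as they are.

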### Recruitment {15}

Clinical trial recruitment involves the screening of patients in Acharya Vinoba Bhave Rural Hospital, Obstetrics and Gynaecology Ward, identifying eligible participants who fulfill the eligibility criteria (inclusion and exclusion criteria) and with written informed permission from willing participants.

## Assignment of interventions: allocation

### Sequence generation {16a}

This process involves the allocation of the patient based on randomly generated numbers. The patient is required to select an envelope containing numbers. The patient’s assignment to the type of intervention will depend on the number.

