### Concealment mechanism {16b}

#### Basic random sampling

The study participants will be randomly assigned using computer-generated random numbers. Randomization is guaranteed through computer-generated random numbers placed in opaque envelopes, ensuring unpredictability and equal chance of group assignment; this method minimizes selection bias as the sequence is pre-determined and concealed. Basic random sampling via these computer-generated numbers further supports balanced allocation across the two groups.

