### Implementation {16c}

A blind individual without any medical training will create the random number sequence. Participants will be enrolled and assigned to the interventions by the study’s primary investigator.

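### The protocol describes two incompatible ways of allocating patients, and the random method it names does not secure the balance it claims

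*Protocol article*

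**What the plan says.** Four places in the protocol article bear on allocation.

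- **Sequence generation {16a}**: "The patient is required to select an envelope containing numbers". And: "The patient’s assignment to the type of intervention will depend on the number".
- **Concealment mechanism {16b}**: computer-generated numbers go into opaque envelopes, and "this method minimizes selection bias as the sequence is pre-determined and concealed". The section adds: "Basic random sampling via these computer-generated numbers further supports balanced allocation across the two groups".
- **Implementation {16c}**: a separate person without medical training creates the number sequence. Then: "Participants will be enrolled and assigned to the interventions by the study’s primary investigator".
- **Sample size {14}**: a 1:1 ratio, with 23 given as the minimum for each group and 46 in total.

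Elsewhere the principal investigator takes consent (section 26a), gives or oversees the interventions in hospital (section 11c), and is in charge of randomisation (section 5d).

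The article names no blocks, no fixed pool of envelopes, no numbering on the outside of the envelopes, and no rule that turns a number into an arm.

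**The concern.** A pre-determined sequence protects a trial because the arm due to the next patient is settled before that patient is known, and because anyone can later compare what was given with what the list required. A free choice among envelopes gives up the second property: there is no next entry, only whichever envelope was picked. The protocol claims the safeguard of the ordered list but describes a draw.

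The roles make this material. One investigator consents, enrols, assigns, and gives or oversees treatment, so an allocation that can be verified against a list is the natural counterweight.

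The second part concerns the balance statement. Simple random numbers give each patient an equal chance of either arm. They do not give equal arms, and the sample size section sets a minimum for each arm.

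**Working it through.** **Step 1. The two procedures side by side.** Suppose the generated sequence is the ordered list a1, a2, …, a46.

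- Under Concealment mechanism, patient *i* should receive a*i*.
- Under Sequence generation, patient *i* receives the content of whichever envelope the patient selects.

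These agree only if selecting an envelope means taking the next one in order, and the text does not say so. Under a free draw one can at most confirm that a number belonged to the generated set. One cannot confirm that it was the number due to that patient.

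**Step 2. Reproduce the planned sample size.** Inputs, all from Sample size {14}: two-sided α = 0.05, power 0.80, means 7.916 and 5.983, SDs 2.256 and 2.327, ratio 1:1.

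- Difference = 7.916 − 5.983 = 1.933, and its square is 3.736.
- Sum of variances = 2.256² + 2.327² = 5.090 + 5.415 = 10.504.
- n = (1.960 + 0.842)² × 10.504 / 3.736 = 22.07, rounded up to 23 per group and 46 in total.

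The stated figure reproduces. The z-value for power is printed as 0.084. Taken literally it would give (1.96 + 0.084)² × 10.504 / 3.736 = 11.7, or 12 per group, so it is a misprint for 0.84 and did not affect the stated size.

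**Step 3. Balance if allocation is simple.** *Assumption: basic random sampling means independent 1:1 assignment of each patient.* The size X of one arm is then Binomial(46, 0.5).

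- P(23:23) = C(46, 23) / 2⁴⁶ = 11.7%.
- P(one arm below 23) = 100% − 11.7% = 88.3%.

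| Split or more uneven | Probability |
|---|---|
| 20:26 | 46.1% |
| 18:28 | 18.4% |
| 16:30 | 5.4% |

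*Alternative assumption: a fixed pool of 23 + 23 envelopes drawn without replacement.* The split is then 23:23 with certainty once all 46 are used.

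**Step 4. What an uneven split costs in power.** Two-sample t-test, noncentral t with 44 degrees of freedom. Common SD = √(10.504 / 2) = 2.292. Noncentrality = 1.933 / [2.292 × √(1/n₁ + 1/n₂)].

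| Split | Power |
|---|---|
| 23:23 | 79.9% |
| 20:26 | 79.2% |
| 18:28 | 78.0% |
| 16:30 | 76.0% |

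Averaged over all splits under simple randomisation, power is 79.0%. The expected loss is therefore about 1 percentage point.

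**The case against.** The strongest reply has four parts.

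*The numbers are generated beforehand by someone else and placed in opaque envelopes, so the contents are fixed and hidden before anyone draws.* This stands in part. A free draw from shuffled opaque envelopes can be random, and it does not reveal the next assignment. It still does not follow a sequence, which is the property the protocol relies on.

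*Nothing says that randomisation is unrestricted.* This stands. The reading rests on the term basic random sampling and on the absence of any named restriction. The percentages in Step 3 are therefore conditional. The conflict between a free draw and an ordered sequence does not depend on them: it is present with a fixed pool as well.

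*The balance sentence speaks of support, not a guarantee, and imbalance costs little.* The small cost is confirmed by Step 4. The sentence still credits the method with a property that it has only on average.

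*A journal article leaves envelope logs and similar details to the full protocol.* This is accepted, and the absence of such details is not counted here. The point rests on what the article states in sections written for this purpose.

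A reader might also infer that mixing emergency and elective sections without stratification is an error. The documents do not support that. Eligibility admits both types, no passage promises balance between them, and neither their mix nor their effect on outcome is given.

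**Conclusion.** The point holds in two parts.

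1. The procedure in Sequence generation and the safeguard in Concealment mechanism cannot both be carried out as written. The two sections must be reconciled. This is the weightier part, because allocation underlies the trial's only between-group comparison and a fault in it cannot be repaired in the analysis.
2. The balance statement is wrong as a description of simple randomisation. Under that assumption at least one arm misses the stated minimum of 23 in 88.3% of trials of 46. The consequence for power is minor: about 1 point on average and about 2 points at 18:28.

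A reader might go further and conclude that concealment has failed, or that allocations can be manipulated without trace. The documents do not support this. They specify opaque envelopes and a separate sequence generator, and they are silent, rather than permissive, about redraws, discarded envelopes and record keeping. What can be said is narrower: a free draw leaves no ordered list to check against, in a trial where one investigator enrols, assigns, and gives or oversees treatment.

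**What to change.** Replace the text under Sequence generation and Concealment mechanism with one procedure:

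- Remove the patient's choice of envelope.
- Have the person who already creates the sequence prepare a restricted 1:1 list, for example permuted blocks of varying size that are not disclosed to the investigator. Even block sizes can be made to sum to the target: 7 × 4 + 3 × 6 = 28 + 18 = 46, which ends at 23:23.
- Place the assignments in sequentially numbered, sealed, opaque envelopes.
- Open them strictly in order, only after consent and all baseline scores are recorded, and write the participant ID and date on the envelope before opening it.
- Keep the list so that allocations can be compared with it.
- Delete the statement that basic random sampling supports balance.

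**Cost.** Slightly more preparation by the sequence generator and a rewritten paragraph. Under the protocol's own amendment section, a change of method also goes to the ethics committee and, if major, to the registry. No extra staff or patients are needed.

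**Downside.** The investigator knows past assignments, so blocks make some late-block assignments easier to guess. Varying, undisclosed sizes limit this. A single random ordering of 23 + 23 in numbered envelopes is an alternative that also reaches 23:23 at 46, but it controls balance less well if recruitment stops early.

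Stratifying by emergency or elective section is optional and not needed to correct the error. If it were adopted together with adjustment for section type, the planned t-test or Mann–Whitney comparison and the statement that no adjusted analysis is planned would also have to change.

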### Concealment mechanism {16b}

#### Basic random sampling

The study participants will be randomly assigned using computer-generated random numbers. Randomization is guaranteed through computer-generated random numbers placed in opaque envelopes, ensuring unpredictability and equal chance of group assignment; this method minimizes selection bias as the sequence is pre-determined and concealed. Basic random sampling via these computer-generated numbers further supports balanced allocation across the two groups.

### Implementation {16c}

A blind individual without any medical training will create the random number sequence. Participants will be enrolled and assigned to the interventions by the study’s primary investigator.

## Assignment of interventions: blinding

### Who will be blinded {17a}

Outcome accessor would be blinded to the intervention.

### Procedure for unblinding if needed {17b}

No unblinding is permissible to reduce the risk of bias.

## Data collection and management

### Plans for assessment and collection of outcomes {18a}

Baseline assessment: Before giving any intervention, data will be collected from subjects at the beginning of the first week.Intervention period: During the 4 weeks of the intervention, subjects will get both the relaxation technique (Benson’s and Mitchell’s), along with the conventional physiotherapy exercises.Post-intervention assessment: After the fourth week of intervention, right after the intervention period, data will be gathered once again.

### Plans to promote participant retention and complete follow-up {18b}

#### Daily follow-up

To keep subjects engaged and track adherence, they will be contacted every day throughout the intervention period.

#### Pre- and post-intervention assessments

Clear checkpoints for retention and result measurement are provided by the data collection at baseline (beginning of week 1) and at the conclusion of the intervention (end of week 4).

#### Regular intervention schedule

To promote routine and subject commitment, both groups receive conventional physiotherapy exercises and a 30-min relaxation technique 5 days a week.

### Data management {19}

The frequency percentage for qualitative data and the mean and standard deviation for quantitative data will be used to summarize the information acquired.

### Confidentiality {27}

Any information about the subjects participating in the study shall be maintained confidential. Any patient-related information will only be used with due permission from the subjects.

### Plans for collection, laboratory evaluation, and storage of biological specimens for genetic or molecular analysis in this trial/future use {33}

Not applicable.

